### Data management {19}

The data, which include the completed informed consent form, testing notes, electrical testing data, and printed testing data, will be carefully filed and securely stored in the researcher’s office at the University of Ottawa. The computer in the researcher’s office will also be locked to limit the access. The data will be encrypted and stored in the password-protected and password-encrypted computer of the researcher. The computer will be locked to limit the access. A number code system will be employed during the data collection, analysis, and reporting. In addition, only the researchers can access the number code system in relation to the data obtained from the participants (e.g., electronic data, the master sheet). The master sheet that links the participants’ identification to their number code and other data documents will be kept in a locked filing cabinet of the PI’s office.

### Confidentiality {27}

Information from the study will be held in strict confidentiality and will not be used except for research purpose. The information collected in the study will be coded with anonymity. Any published results will be presented with complete anonymity. Any personal (e.g., address and telephone number) and testing data will be kept in a separate file folder, accessible only by the researchers responsible for the project. The data will be conserved for a period of 5 years after the time of publication. After the time of publication, all the electronic data will be permanently deleted from the computer. The printed data file will be shredded.

### Plans for collection, laboratory evaluation, and storage of biological specimens for genetic or molecular analysis in this trial/future use {33}

N/a.

## Statistical methods

### Statistical methods for primary and secondary outcomes {20a}

Statistical analysis will be performed using SPSS 20.0 and Microsoft Excel 2019 software. Each of the measures will be expressed as mean ± standard deviation. If a measure is not normally distributed, the median and IQR will be calculated to characterize the non-normal distribution. The stratification factors (i.e., age and gender) will be accounted for by an appropriate adjustment technique, such as ANCOVA or multivariable regression analysis. Analysis will be performed to the measures obtained from baseline and at 6 and 12 weeks after TC training. Then, the data between the TC and PA groups will be compared. Two-way analysis of variance (group × time) with repeated measures will be used for examining the effect of TC training on the primary and secondary outcomes. The participants will be analyzed based on their initially allocated groups via randomization, regardless of whether they adhere or if they received the allocated intervention. Statistical significance will be set at *p* less than 0.05.

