### Sample size {14}

The estimated number of participants to achieve the study’s objectives is 40, calculated to attain a 93% statistical power in the difference between two means of the independent variables for testing hypotheses with an alpha level of 5% and a minimal clinical important difference (MCID) of 1.13. This estimation is based on the calculation of the minimal clinical important difference that was determined based on the values obtained in past published studies [13, 26–28]. Considering a 10% of dropout rate of the participants recorded from a previous 24-week TC intervention study for those with PD [13], a 5% dropout rate is expected.

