### Methods in analysis to handle protocol non-adherence and any statistical methods to handle missing data {20c}

All data will be thoroughly checked for completeness. Should data be missing from any of the gait or obstacle crossing trials, every effort will be made to locate it first before those cases with the missing data will be dealt with using multiple imputation.

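### The group × time ANOVA names no deciding effect or visit, treats baseline as an outcome, and is not the comparison that the trial was powered on

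*Protocol article*

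**What the plan says.** - **Model.** Statistical methods {20a} applies a two-way (group × time) analysis of variance "with repeated measures will be used for examining the effect of TC training on the primary and secondary outcomes". The measures analysed are those from baseline, week 6 and week 12. Neither the group main effect, the interaction nor a contrast at a given visit is named as decisive.
- **Adjustment.** The same section adjusts for age and gender by ANCOVA or regression. The baseline value of the outcome is not named as a covariate. The sections on blinding {17a} and additional analyses {20b} say that changes are judged against each participant's own baseline, but give no baseline-adjusted model.
- **Analysis set.** "The participants will be analyzed based on their initially allocated groups via randomization, regardless of whether they adhere" ({20a}).
- **Missing data.** Section {20c} plans multiple imputation, introduced by the words "Should data be missing from any of the gait or obstacle crossing trials".
- **Power.** Sample size {14}: "The estimated number of participants to achieve the study’s objectives is 40, calculated to attain a 93% statistical power", for "the difference between two means", with "a minimal clinical important difference (MCID) of 1.13". It expects 5% dropout.

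**The concern.** With three visits, the group × time interaction asks whether the two mean profiles differ in shape in any way. It is one test on 2 degrees of freedom, and baseline is part of it. This has three consequences.

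1. A significant result does not say at which visit the groups differ. A difference at week 6 that has vanished by week 12 can produce it, so the test does not by itself establish an effect at the end of the 12-week programme.
2. The stated power belongs to a different test.
3. Baseline is used as an outcome level, where randomisation makes the expected group difference zero. Used as a covariate, it would reduce the error variance at week 12.

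Because no effect or visit is named, the choice between interaction, main effect and visit-wise comparison stays open until the results are seen. Classical repeated-measures ANOVA also needs all three visits for each participant, so the commitment to analyse participants as allocated depends on how far the imputation reaches.

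**Working it through.** **Inputs from the protocol article:** 40 participants, 1:1, so 20 per arm; 5% dropout leaves 40 × 0.95 = 38, or 19 per arm; alpha 5%; difference 1.13; visits at baseline, week 6 and week 12.

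**Assumptions, not in the document:** two-sided test; 1.13 in SD units; equal variances and the same correlation ρ between any two visits (compound symmetry); ρ from 0.3 to 0.8; the time course of the effect. Adjustment for age and sex is left out throughout.

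**1. The plan's own figure.** Two-sample t-test, noncentrality d√(n/2), df 2n − 2.
- 20 per arm: 1.13 × √10 = 3.573, df 38, power 93.6%.
- 19 per arm: 1.13 × √9.5 = 3.483, df 36, power 92.3%.

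The stated 93% is therefore reproduced as one comparison of two means.

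**2. The planned interaction against a week-12 ANCOVA, 19 per arm.** Interaction: λ = (n/2) Σ(δ − mean δ)² / (1 − ρ), df 2 and 2(2n − 2) = 72. With linear growth the group differences are 0, 0.565 and 1.13, the sum of squares is 2 × 0.565² = 0.638, and λ = 9.5 × 0.638 / (1 − ρ). ANCOVA on baseline: noncentrality 3.483 / √(1 − ρ²), df 35.

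| ρ | λ | Interaction | ANCOVA noncentrality | Week-12 ANCOVA | Week-12 t-test |
|---|---|---|---|---|---|
| 0.3 | 8.66 | 73.5% | 3.651 | 94.4% | 92.3% |
| 0.5 | 12.13 | 87.3% | 4.022 | 97.4% | 92.3% |
| 0.7 | 20.22 | 98.2% | 4.877 | 99.7% | 92.3% |

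**3. How far this depends on the assumptions (19 per arm).**
- 1.13 SD with the full effect already at week 6: interaction 85.5%, 95.1% and 99.7% at ρ 0.3, 0.5 and 0.7.
- 0.8 SD, linear growth: interaction 43.1%, 57.1% and 80.4%; ANCOVA 71.0%, 79.1% and 91.9%; t-test 67.0%.
- 0.8 SD, ρ 0.8, full effect at week 6: interaction 98.3%, ANCOVA 97.9%. There is no loss.

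**4. An effect at week 6 only.** Differences 0, 0.8 and 0 SD: the sum of squares is 0.427, and λ = 5.79, 8.11 and 13.51 at ρ 0.3, 0.5 and 0.7. The interaction is significant in 54.9%, 70.4% and 90.7% of trials, although the groups do not differ at week 12.

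**5. The group main effect is no substitute.** It averages in baseline. With linear growth to 1.13 SD the mean difference is (0 + 0.565 + 1.13)/3 = 0.565, and the SD of a participant's mean is √((1 + 2ρ)/3). At 20 per arm, power is 66.4%, 56.9% and 49.5% at ρ 0.3, 0.5 and 0.7.

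**6. Reach of the imputation.** COM-COP separation, toe and heel clearance, gait speed, cadence and step length all come from the walking and obstacle-crossing trials, so the imputation in {20c} applies to them. Its wording concerns data missing from trials and does not clearly say whether a wholly missed visit is included. UPDRS-III, TUG, single-leg stance, TMT-B, WCST and Stroop are not gait or obstacle-crossing trials, and no method is stated for them.

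**The case against.** Three stronger readings are tempting, and the document does not support them.

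- **That the primary analysis drops participants with a missing visit and so breaks the as-randomised commitment.** Multiple imputation is the stated plan for the data from which the primary outcomes come. Once the data are imputed, the ANOVA has no incomplete case to drop. Even for the clinical and cognitive outcomes, complete-case analysis is an inference from silence. A loss of about 10% would require 5% missing independently at each of two follow-up visits (1 − 0.95² = 0.0975); the protocol gives 5% dropout.
- **That the planned test always loses power.** It does not. At ρ 0.7 with linear growth to 1.13 SD, the interaction (98.2%) exceeds the two-mean comparison (92.3%) and nearly equals ANCOVA. With the full effect by week 6 and ρ 0.5, its 95.1% also exceeds the t-test.
- **That significance from a week-6 difference is a false positive.** The hypothesis names no visit and both follow-ups are analysed, so a true week-6 difference is a real effect. The percentages in step 4 are power to detect it. What stands is that such a result does not show an effect at week 12.

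It can also be said that comparing change from baseline is valid under randomisation, and that visit-level contrasts and intervals are often left to a fuller document. Both are fair: ANCOVA is a gain in efficiency, not a cure for bias. But the article commits to a named test, and that test matches neither the sample-size calculation nor an end-of-intervention question.

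**Conclusion.** The point holds in a limited form. No deciding effect or visit is fixed, baseline is not named as a covariate, and the 93% is not the power of the planned interaction.

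Under linear growth to 1.13 SD with 19 per arm, the interaction falls short of week-12 ANCOVA by about 21 points at ρ 0.3 (94.4 − 73.5), 10 at ρ 0.5 (97.4 − 87.3) and 1.5 at ρ 0.7 (99.7 − 98.2). The gap is negligible at 1.13 SD with ρ 0.7 or more, and also at ρ 0.8 if the full effect is present by week 6. At 0.8 SD with linear growth it is still 11.5 points at ρ 0.7 (91.9 − 80.4). All of this rests on reading 1.13 as SD units and on an assumed correlation and time course.

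The lack of a named comparison does not depend on those assumptions. On missing data, what remains is unclear coverage of wholly missed visits and no stated method for the clinical and cognitive outcomes.

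**What to change.** Replace the repeated-measures ANOVA in {20a} with a linear mixed model on the week-6 and week-12 values. Its terms are the baseline value of the outcome, age, sex, group, visit and group × visit, with unstructured covariance within participant. For each primary outcome, the primary result is the adjusted TC minus PA difference at week 12 with its 95% CI; week 6 is supportive. Use the same model for the other continuous outcomes.

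In {20c}, state how wholly missed visits are handled for every outcome, either by extending the imputation to them or by relying on the mixed model. Participants with no follow-up at all contribute nothing to that model, so keep them through imputation or a sensitivity analysis.

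The cost is new wording before the data are analysed. No new data are needed, and standard software fits the model. The one drawback is that a transient effect seen only at week 6 no longer counts as the primary result.

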### Interim analyses {21b}

N/a.

### Methods for additional analyses (e.g., subgroup analyses) {20b}

No planned subgroup analyses were involved in this study. Gender differences are anticipated to be present, but these differences are not one of the primary outcomes of interest or one of the effects of TC training. We do not anticipate any gender effects to remarkably contribute to the effects of TC training. Efforts were made to ensure that only the effects of TC training are examined, by making the intervention groups comparable, setting a strict age range for the participants’ age, and using the individual’s baseline scores for comparisons with their post-training evaluations. Accordingly, we will strictly examine the potential mechanisms and training effects of TC for symptoms related specifically to PD.

### Methods in analysis to handle protocol non-adherence and any statistical methods to handle missing data {20c}

All data will be thoroughly checked for completeness. Should data be missing from any of the gait or obstacle crossing trials, every effort will be made to locate it first before those cases with the missing data will be dealt with using multiple imputation.

### Plans to give access to the full protocol, participant-level data, and statistical code {31c}

Public access will be granted to the full protocol, participant-level dataset, and statistical code upon request.

## Oversight and monitoring

### Composition of the coordinating center and trial steering committee {5d}

The thesis (or steering) committee of the PhD candidate, who will be responsible for conducting and overseeing this study, will guide and provide feedback to develop and refine the details of the study. The thesis committee includes Drs. [name] and [name]. This committee will ensure that the quality of the candidate’s work meets all academic regulations and requirements for completion of the candidate’s degree. The committee will review the candidate’s work for publications, travel applications, and application funds for conferences and seminars.

### Composition of the data monitoring committee, its role and reporting structure {21a}

A data monitoring committee is not needed, because this role will be fulfilled by the thesis (steering) committee.

### Adverse event reporting and harms {22}

Participants will be allowed to take breaks or rest whenever they prefer. If the participants feel physically exerted, they will be allowed time to rest and water or other forms of rehydration methods would be provided to them. Prior to the performance of the TC routine, the participants will go through a proper warm-up that will involve some basic (light) stretching, breathing, and warm-up movements for the upper and lower extremities. This activity would help mitigate any undesired muscle fatigue, discomfort, or soreness. To reduce the risk of falls or related injuries, the TC instructor, and/or the researchers will be available to monitor the performance of each participant. For participants that are deemed at a higher risk of falling, a spotter will be provided upon either request by participant or if it is evident to the instructor/PI that a spotter is needed. All serious injuries/harm resulting from either the laboratory testing or TC intervention and PA engaged by the participants will be reported to the PI and Research Ethics Board (REB) of the University of Ottawa.

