## Introduction

### Background and rationale {6a}

Parkinson’s disease (PD) is a growing concern in Canada, where approximately 100,000 people are living with PD; this number is expected to rise to 163,700 by 2031 [1]. The direct and indirect socioeconomic costs in Canada associated with this neurological condition are estimated to be more than $1.214B [2]. Postural instability and gait difficulties are common problems reported among people with PD [3, 4]. People with PD have difficulties with daily tasks such as walking caused by gait-related changes in step width and step length that can lead to reduced walking speeds. This “cautious gait” approach is similar to older adults who are at a high risk of falls [5, 6]. Falls and the loss of the ability to live independently are among the key concerns of people with PD. A 1-year follow-up study among 109 subjects with idiopathic PD diagnosed according to the brain bank criteria reported a fall occurrence of 68.3% [7].

Exercise intervention programs are being used in conjunction with drug therapy (such as levodopa, carbidopa) as standard of care to manage the symptoms related to PD [8, 9]. Tai Chi (TC) is a body-mind exercise that has been recommended by *Parkinson’s Canada* as one of the few exercise programs specific for those with PD [10]. TC training is suggested to help improve the awareness of whole-body movement and joint proprioception and increase muscle strength and endurance of the lower limb, thus strengthening the neuromuscular reaction of muscles in the lower extremities [11, 12]. For people with PD, TC training would help in challenging postural stability, particularly in the mediolateral (M-L) direction that is closely related to fall prevention. It will also strengthen the muscles at the hip involved in postural control. Regular TC practice and training would lead to improvements in gait and postural stability by encouraging weight shifting, control displacement of the COM over the base of support, and comfort with stepping in different directions.

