## TC training group

For the TC group, the first 2 weeks of the program will require the participants to work on some light breathing and simple upper-limb forms. The basic TC forms will be introduced with a focus on becoming comfortable with the flow and rhythm of the movements. Each session will run for 60 min and will be supervised by a TC instructor in a community center. The training will be gradual and range from low to moderate intensity. Participants will warm up for 5–10 min, perform core activities for 40 min, and cool down for 5 min. Three sessions will be offered weekly for 12 weeks; the participants will be asked to attend at least two sessions per week. The third to sixth week of the program will focus on incorporating the upper and lower limb into the routine. These classes will focus on practicing the seven TC forms sequentially. The six remaining weeks of the program will focus on repetitions and performance mastery of the basic seven-form routine. The participants will be allowed to practice TC at home. Any TC that the participant performs in their home or on their own time will be recorded by themselves by using a monitoring form that will be distributed to them and collected weekly. The TC instructor will be present at each of the session to monitor the participants’ progress and to ensure that the movements are being performed correctly.

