## Physical activity group

The PA group will track their level of PA over 12 weeks. During this period, the participants will be required to engage in at least 60 min of regular PA on their own for three times per week. Regular PA may include walking, cleaning, performing chores inside the home, and/or climbing the stairs. No restriction will be made to limit other forms of PA. Individuals in the PA group will be permitted to engage in organized sports and instructor-led class such as boxing and dance to ensure that the participant recruitment process is feasible. An active control group was used for comparisons between the groups who will or will not receive formal TC training and to reflect the daily lifestyle and activities of a typical individual with PD from the community. Similar to the TC group, the participants in this group will be asked to complete an activity log form for monitoring, and this form will be collected weekly to monitor their regular PA levels.

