TC, as a “mind–body” exercise, has been applied to manage PD-related symptoms and has increased in popularity because of its rehabilitative potential. TC training shares many features as rhythmic exercises such as tango and ballroom dance that focus on the timing of the participant’s foot placement, whole body coordination, and awareness and attention to their own and partners’ movement [38]. TC is a form of martial art that has been recommended by the *American Geriatric Society* and *British Geriatric Society* for fall prevention in the elderly [39]. However, these activities are only general recommendations that are provided without the proper training protocols and guidelines for those with PD who wish to use TC as a form of therapy or exercise to maintain their physical health and wellbeing. Previous TC programs for PD have demonstrated beneficial effects on posture, gait, and mobility, but limited information is available about the selection basis of TC movement. The mechanisms in the beneficial effects of TC training on gait and postural stability for people with PD are unknown. MRI results have provided support to the beneficial effects of TC practice on brain structure and cognition function [40]. More research on TC intervention on gait, postural stability, and cognition function would improve the understanding of the effects of practicing TC in PD and to access its role and safety as an effective form of exercise to improve quality of the life of this population.

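### The stated harms rule covers only serious, activity-related events and only the Tai Chi arm is supervised, so other falls have no reporting rule and harm counts by arm would rest on unequal observation

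*Protocol article*

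**What the plan says.** The section on adverse event reporting and harms {22} is mostly about prevention: rest, hydration, warm-up, spotters and monitoring. Its one commitment on reporting reads "All serious injuries/harm resulting from either the laboratory testing or TC intervention and PA engaged by the participants will be reported", with the principal investigator and the university's ethics board as recipients. It also says: "To reduce the risk of falls or related injuries, the TC instructor, and/or the researchers will be available to monitor the performance of each participant".

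The two arms are observed differently.

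- **TC arm** (section on the TC training group): "Each session will run for 60 min and will be supervised by a TC instructor in a community center", and "The TC instructor will be present at each of the session". Three sessions a week are offered. Practice at home is self-recorded "using a monitoring form that will be distributed to them and collected weekly". The section on retention {18b} adds that the instructor, investigator and/or research assistants are present at training and laboratory testing.
- **PA arm** (section on the physical activity group): participants do their activity on their own three times a week and fill in an activity log; "this form will be collected weekly to monitor their regular PA levels". The section on adherence {11c} repeats the weekly collection.

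Both arms visit the laboratory at baseline, 6 and 12 weeks. Neither weekly form is said to ask about falls or injuries, and falls are not among the outcomes in the section on outcomes {12}.

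The background {6a} motivates the trial by fall risk. It cites a one-year study of 109 people with Parkinson's disease that "reported a fall occurrence of 68.3" percent.

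**The concern.** The published rule applies two filters, seriousness and attribution. An event that fails either one comes under no stated reporting rule. In this population the obvious example is a fall without serious injury, or a fall at home that nobody links to the study. Since falls are not an outcome, harm reporting is the only route the article describes by which they could come to light.

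Events that do qualify still have to be noticed. In the TC arm a member of the trial team is in the room during sessions. In the PA arm nobody from the trial is present during the activity, and the stated purpose of the log is to track activity levels. Any table of harms by arm built on this reporting would reflect how closely people were watched and how events were labelled, as well as what the treatment did. The primary analysis of gait and postural stability is not affected. What is at stake is whether the trial can describe falls and injuries at all, and whether a reader could interpret such a description by arm.

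**Working it through.** The article states no figure on harms, so there is nothing of its own to reproduce on this point. The check has three parts.

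**1. Which events the rule reaches**

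| Event | Serious? | Attributed to testing, TC or PA? | Stated reporting rule? |
|---|---|---|---|
| Serious injury in a TC class | yes | yes | yes |
| Serious injury during logged PA | yes | yes | yes |
| Fall in class without serious injury | no | yes | none |
| Fall at home without serious injury | no | no | none |
| Serious fall judged unrelated to the study | yes | no | none |

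**2. How many fallers there might be (illustration)**

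Inputs: 68.3% in one year (background {6a}); 12 weeks of follow-up (trial design {8}); 40 participants (sample size {14}), 20 per arm at 1:1. Assumptions: the 68.3% is the proportion of people who fell at least once, the hazard is constant, and the figure carries over to this sample.

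- Formula: p(12 weeks) = 1 − (1 − p(1 year))^(12/52)
- At the cited figure: 1 − 0.317^(12/52) = 0.233. Times 40 = 9.3 people; times 20 = 4.7 per arm.
- At half the annual figure, 34.15% (assumed, as a lower case): 1 − 0.6585^(12/52) = 0.092. Times 40 = 3.7 people; times 20 = 1.8 per arm.

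**3. What unequal detection could do**

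Suppose both arms have the same true risk, 4.7 fallers each. The capture rates below are assumptions; the article gives none.

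| Capture TC | Capture PA | Counted TC | Counted PA | Ratio TC/PA |
|---|---|---|---|---|
| 90% | 90% | 4.2 | 4.2 | 1.0 |
| 90% | 60% | 4.2 | 2.8 | 1.5 |
| 90% | 30% | 4.2 | 1.4 | 3.0 |
| 60% | 90% | 2.8 | 4.2 | 0.67 |

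The last row is there because the direction is open:

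- Supervision favours detection in TC. But it fills only 2 to 3 hours a week (at least two of three 60-minute sessions), which is 2/112 = 1.8% to 3/112 = 2.7% of an assumed 112 waking hours. Most falls in either arm would happen unobserved.
- Attribution may pull the other way. Regular PA includes chores, cleaning and stairs, so a serious fall during housework could count as resulting from PA in the control arm. The same fall in a TC participant need not count as resulting from TC. The rule does not say whether its reference to PA covers both arms.

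**The case against.** The best case for the plan has five parts.

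- **Weekly contact is equal.** A reader might infer that the PA arm goes unwatched from week to week. The article does not support that: the log is collected weekly, both arms attend the same laboratory visits, and PA participants may join instructor-led classes. The difference is direct supervision by the trial, nothing broader. This objection stands.
- **No safety comparison is planned.** A reader might infer that a planned comparison is biased. Falls and harms are not outcomes, and the statistical methods {20a} describe no analysis of harms by arm. The discussion's phrase "to access its role and safety as an effective form of exercise" belongs to a sentence about what more research in general would add, and is not an aim of this trial. This stands too. The point concerns any counts that come to be reported by arm.
- **Reporting is not recording.** The sentence says what goes to the investigator and the ethics board, and a condensed article may omit a wider collection procedure. That is fair, so the claim that lesser events will go unrecorded is not made here. What remains is that the rule actually printed is narrow. If the full protocol is wider, the sponsor need only say so.
- **The direction is unknown.** A reader might conclude that TC will look worse. Supervised time is short and attribution could work against the PA arm, so that conclusion is not supported.
- **The fall figure may not transfer.** Participants are at Hoehn and Yahr stages 1 to 3, without motor fluctuations, walk independently and are screened for cognition. A lower rate is plausible, which is why half the cited figure is also shown.

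**Conclusion.** The concern holds in a limited form. As published, the harms rule reaches only serious events that result from testing, TC or PA. Falls and injuries outside those limits have no stated reporting rule in a trial motivated by falls. Because only TC is directly supervised by the trial and neither weekly form is said to ask about harm, counts by arm would be open to unequal ascertainment of unknown direction.

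The illustrative size is about 9 of 40 people falling in 12 weeks at the cited rate, or 3 to 4 at half of it. Both assume a constant hazard and that the cited study's population applies. It would be tempting to add that most of these falls would go uncounted; the article gives no figure for how many are serious or attributed, so that is an inference and not a finding.

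This is a cheap improvement to safety information. It is not an error in the efficacy analysis.

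**What to change.** Add the same fixed question to both forms already collected each week (the TC monitoring form and the PA activity log): the number of falls, injuries and other health problems in the past week, wherever they happened. Use identical wording and the same recall period in both arms, and ask it of every TC participant each week, whether or not they practised at home.

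Report all events from this source by arm in one descriptive table, regardless of seriousness or attribution. Keep events noticed only by the instructor out of the between-arm table, so that both columns come from the same source. With so few expected fallers per arm, no test is needed.

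Leave the existing reporting of serious harm to the principal investigator and ethics board unchanged. If the full protocol already collects all events by an identical prompt in both arms, a sentence saying so would be enough.

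Cost: one question on each of two forms, the work of aligning forms that currently serve different purposes, a small weekly burden on participants, and one table.
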